#### Population-level N-of-1 trial analysis

For the population-level assessment of the PPGR to different staple foods, a Bayesian generalized linear mixed regression model will be used to aggregate the results from multiple *N*-of-1 trials at the population level, incorporating both between-individual and within-individual variations. Individual regression models will be linked using a random-effects model, assuming that the individual-specific regression coefficients follow a normal distribution centered on the population’s average coefficient. Noninformative priors will be used to define the variance distribution of the parameters, ensuring the robustness of the analysis. The threshold for posterior probabilities will be set at 80%. Additionally, the posterior probability of the mean differences exceeding the MCID will be evaluated.

#### Exploratory analysis

To investigate the role of gut microbiota in modulating glycemic responses to staple foods, the baseline metagenomic data will first undergo quality control filtering to exclude microbial features with low prevalence (species detection rate < 5%). Microbiota significantly associated with WGRS (*P* < 0.05) will then be preliminarily identified using Spearman correlation analysis, followed by the application of LASSO regression with 10-fold crossvalidation to compress high-dimensional data and identify core species. To further explore the relationship between gut microbiota characteristics and WGRS, a mixed-effects model will be constructed, with WGRS as the dependent variable, the screened microbiota features and covariates (e.g., age, gender, BMI, smoking, and alcohol consumption) as fixed effects and subject ID as a random intercept to account for individual variability. Additionally, the microbiota × staple food interaction term will be introduced to evaluate the potential regulatory effect of microbiota on staple food-specific glycemic responses, with multiple comparisons adjusted using the Benjamini-Hochberg false discovery rate correction at a significance threshold of <0.15.

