### Sample size estimation

In this study, the primary outcome, PBGP, was reported at the population level using a Bayesian hierarchical model. Given the absence of formulas for sample size calculation in this type of population design, the sample size calculation in this study referred to the simulation method based on the Bayesian hierarchical model conducted by Stunnenberg et al. [23]. Additionally, the statistical power under different sample sizes was evaluated via the Markov Chain Monte Carlo (MCMC) method. The minimum clinically important difference (MCID) is an indicator used to assess the clinical significance of changes in medical outcomes [24]. It represents the smallest change in clinical outcomes that is considered meaningful by patients, clinicians, or researchers. Referring to the study by Tian et al. [25], the MCID of PBGP in this study was defined as 0.78 mmol/L, which was determined based on a 20% difference in PBGP between patients with T2DM and those with impaired fasting glucose, i.e., 3.89 mmol/L [26]. According to previous studies, the difference in PBGP between patients with diabetes consuming white rice and pasta was 2.4 mmol/L, with a between-individual SD of 2.5 mmol/L and a within-individual SD of 1.2 mmol/L [21]. At the individual level, it was assumed that the true intervention effect of each participant followed a normal distribution; at the observation level, the within-individual variation was set to be the same. Observational data for each subject were randomly generated through simulation involving 3 intervention cycles and 5 staple foods, and a Bayesian hierarchical model was constructed based on these data.

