The calculation process was implemented using JAGS 4.3.0 software. Four independent MCMC chains were set up, with each chain performing 1000 burn-in iterations to eliminate dependence on initial values, followed by 4000 sampling iterations. The convergence of the posterior distribution was ensured through diagnostics using the Gelman-Rubin statistic and autocorrelation function. The criterion for determining clinical significance was set as a threshold where the posterior probability that the population effect exceeded the MCID was >80%. Simultaneously, the type I error rate under the condition of a null effect was evaluated to ensure that the false-positive rate was controlled below the nominal level (α = 0.05). Systematic simulations revealed that when the sample size reached 14, the statistical power to detect the effect size was 86.0%, with a type I error rate of 2.0% at this point, which met the requirements of a target power of 80% and a controllable error rate.

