#### Individual-level N-of-1 trial analysis

To assess the PPGR to various staple foods at an individual level, Bayesian model will be performed. It is presupposed that individual observations of PBGP and iAUC_3h_ adhere to a normal distribution centered on each participant’s true average effect. The MCMC method will be used to estimate the posterior distribution of the parameters of interest. We will initiate 4 chains, with each executing 4000 iterations, culminating in a total of 16,000 sampling iterations. The Bayesian inference will be executed using the following equation for PBGP:(1)$${\text{PBGP}}_{i}=\beta_{0}+\sum_{j}\beta_{j}\cdot {\text{staple}\;\text{food}}_{j}+\epsilon_{i}$$in which the PBGP for participant *i* is modeled as the intercept, with the effect of each staple food *j* denoted as the intervention effect, and the random error for individual *i* modeled as a normal distribution with a mean of 0 and a large SD. Noninformative prior distributions will be incorporated into the model due to uncertainty regarding prior knowledge. Following the estimation of the posterior distribution of the effect of each staple food within the Bayesian model, the average value of the posterior distribution for differences between foods will be calculated, alongside the SE and 95% credible intervals. Standard procedures for warm-up periods, diagnostics for model convergence and stability, and residual checks will be applied. During the warm-up period, initial samples will be discarded to allow the chain to converge to a stationary distribution. The Gelman-Rubin test will be used to assess the convergence of the MCMC chains, with an *R*-hat value of <1.05, indicating that the chain has converged. The threshold for posterior probabilities will be set at 80% [28].

For a comprehensive evaluation of the PPGR of various staple foods among patients with diabetes, a weighted average response probability will be generated for each staple food. Using Bayesian models and sequentially using each staple food as a reference, we will estimate the posterior probability that the average difference between the reference food and the other 4 staple foods exceeds the MCID. As mentioned earlier, in this study, we define the MCID for PBGP as 0.78 mmol/L, and the MCID of iAUC_3h_ is 106.78 mmol/L·min, representing 10% of the difference between patients with T2DM and those with impaired fasting glucose, a difference that amounts to 1067.85 mmol/L·min [29].

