For PBGP, the weighted glycemic response score (WGRS) for each staple food is calculated using the following equation:(2)$${\text{WGRS}}_{i,j}=\frac{\sum_{k\neq j}{P\left({\Delta \text{PBGP}}_{i,j}>0.78\right)}_{k}\cdot \frac{1}{{\text{CV}}_{k}}}{\sum_{k\neq j}\frac{1}{{\text{CV}}_{k}}}$$

Equation 2 computes the sum of the posterior probability that, for participant *i*, the average difference between staple food j and other staple foods *k* exceeds the MCID of 0.78 mmol/L across multiple comparisons, divided by the coefficient of variation (CV) of each staple food *k*, which serves as a weight adjustment [30]. The result is then normalized by the sum of the reciprocals of the CVs. The WGRS of each staple food quantifies the probability of a clinically significant higher PBGP for that food across multiple comparisons. In the context of achieving a more stable glucose response, particularly in patients with diabetes, a staple food with a higher WGRS is less desirable.

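### A random intercept cannot represent the negative within-participant correlation built into WGRS, so the exploratory microbiota-by-food interaction test is somewhat liberal

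*Protocol article*

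**What the plan says.** In the Protocol article, Individual-level N-of-1 trial analysis, Equation 2 defines the WGRS of food j in one participant. It is a weighted mean of posterior probabilities, described as concerning "the average difference between staple food j and other staple foods" and counting differences above the MCID ("we define the MCID for PBGP as 0.78 mmol/L"). Each weight is the reciprocal of the comparator food's CV. A participant thus contributes five scores, all drawn from that participant's own food comparisons.

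Under Exploratory analysis, species are screened by Spearman correlation and LASSO. WGRS then becomes the outcome of a mixed model. Fixed effects are the screened species and participant-level covariates, with age, gender, BMI, smoking and alcohol given as examples. The only covariance term named is "subject ID as a random intercept to account for individual variability". After that, a microbiota-by-food "interaction term will be introduced to evaluate the potential regulatory effect of microbiota". Multiplicity is handled by Benjamini-Hochberg at a threshold of 0.15. The 0.05 level appears only for the Spearman screen.

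**The concern.** A random intercept suits outcomes where some participants run high on every food and others low on every food. WGRS is not such an outcome. It compares foods within a person, so whatever raises one food's score tends to lower another's, and the participant's overall glucose level largely drops out.

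When the true within-participant correlation is negative, the intercept variance is pushed to its boundary at zero and the model becomes ordinary regression on 14 × 5 = 70 rows. Its single residual then averages a small between-participant part with a larger within-participant part. The interaction is a within-participant contrast, so its standard error comes out too small. This is the term from which the protocol would claim that microbiota modify food-specific responses, and its P values feed the Benjamini-Hochberg step.

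**Working it through.** The protocol gives no error rate for this test, so there is no figure of its own to reproduce.

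**Inputs from the Protocol article.**
- Sample size estimation: 14 participants ("when the sample size reached 14, the statistical power to detect the effect size was 86.0%, with a type I error rate of 2.0"%); "simulation involving 3 intervention cycles and 5 staple foods"; "a between-individual SD of 2.5 mmol/L and a within-individual SD of 1.2 mmol/L"; and "the difference in PBGP between patients with diabetes consuming white rice and pasta was 2.4 mmol/L".
- Individual-level analysis: MCID 0.78 mmol/L and noninformative priors. The posterior of a food difference was therefore taken as t with 10 df (15 observations less 5 food means).

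**Assumptions not in the documents.** The SD of individual food effects was varied over 0, 0.5, 1.0, 1.77 and 2.5 mmol/L. The CV was either the raw CV of three values or a near-equal posterior CV. The test was either F or Wald chi-square.

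**Step 1, sign of the correlation.** For any two foods, P(d_jk > 0.78) + P(d_kj > 0.78) = 1 − P(|d_jk| ≤ 0.78). The two probabilities trade off. If the five scores summed to a constant, their average correlation would be −1/(5 − 1) = −0.25. The dead zone within the MCID and the CV weights keep the sum from being constant, so −0.25 is a limit.

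**Step 2, effect on the error term.** With common variance σ² and correlation ρ, the between-participant mean square has expectation σ²(1 + 4ρ) and the within-participant one σ²(1 − ρ). Degrees of freedom with one species:
- within: 13 × 4 − 4 = 48
- between: 14 − 2 = 12, or 7 with five covariates.

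With the intercept variance at zero, the residual is [df_b(1 + 4ρ) + 48(1 − ρ)]σ²/(df_b + 48). The correct error for the interaction is (1 − ρ)σ². F is inflated by roughly their ratio:

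| ρ | df_b = 12 | df_b = 7 |
|---|---|---|
| −0.14 | 1.14/1.00 = 1.14 | 1.14/1.051 = 1.08 |
| −0.23 | 1.23/1.00 = 1.23 | 1.23/1.084 = 1.14 |
| −0.25 (limit) | 60/48 = 1.25 | 55/48 = 1.146 |

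**Step 3, limiting rejection rate at nominal 5%.**
- No covariates: the critical value of F(4, 60) is 2.525, and 2.525/1.25 = 2.020. P(F(4, 48) > 2.020) = 10.7%.
- Five covariates: the critical value of F(4, 55) is 2.540, and 2.540/1.146 = 2.216. P(F(4, 48) > 2.216) = 8.1%.

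**Step 4, simulation.** There were 6000 trials per setting, with scores from Equation 2 and one species unrelated to response. The closed-form balanced REML solution was used, truncated at zero.
- The within-participant correlation of WGRS was about −0.04 to −0.24.
- Intercept variance was zero in 71–100% of trials, and in over 95% once the food-effect SD was at least 1.0.

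| Model, true null, nominal 5% | F test | Wald |
|---|---|---|
| Random intercept, no covariates | 7.1–11.5% | 8.8–13.4% |
| Random intercept, five covariates | 6.5–9.5% | 8.2–11.5% |
| Participant as fixed effect | 4.1–6.9% | not reported |
| Unstructured covariance (Hotelling) | 4.5–5.6% | not applicable |

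A separate simulation agreed: correlation −0.14 to −0.23, zero variance in 97–100% of trials, rejection 6.4–10.5% (F) or 8.1–12.4% (Wald), against 3.9–5.7% with within-participant error only.

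**Step 5, at the protocol's own threshold.** With raw CV, food-effect SD 1.0 and no covariates, the chance of at least one false interaction under Benjamini-Hochberg at 0.15 was 26% with 5 null species and 35% with 20. With participant as a fixed effect it was 16% and 19%.

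**The case against.** Several objections stand in part.

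- **Size.** A reader might infer a flat 8–10% false-positive rate for the planned model. The documents do not support one figure. The listed covariates use up between-participant degrees of freedom, whose pooling causes the inflation. With five covariates and raw CV the F-test range is only 6.5–7.3%. More species in the model lowers the limiting rate further: 8.1%, 7.6% and 6.9% with one, three and five species.
- **Reference level.** A reader might set the excess against 5%. The protocol sets no 5% level for the interaction; its criterion is Benjamini-Hochberg at 0.15. Step 5 shows that the excess carries through to that criterion.
- **Certainty.** A zero intercept variance is usual but not guaranteed. The rates rest on the closed-form solution, because most direct REML fits in standard software failed to give usable results in the re-check (25 and 38 of 400 usable).
- **Other sources of error.** Where food means differ, WGRS variances differ across foods. Part of the excess, up to about 6–7% rejection, then remains even with participant as a fixed effect. Screening on the same data may matter more. If the screen is run per food (an assumption), null species that passed the Spearman step were rejected in about 29% of tests with the random intercept and 20% with participant fixed.
- **Level of detail.** Covariance and df details are often left to a fuller plan. Here, however, the article names both the outcome and the random intercept, and the conflict follows from that stated pair.

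**Conclusion.** The point holds as a limited one. The stated random intercept does not fit the correlation that Equation 2 creates, and the interaction test is liberal as a result. At a nominal 5%, a true null is rejected in about 6.5–9.5% (F) or 8–11.5% (Wald) of trials with the listed covariates, and in up to about 13% without them. The direction follows from the algebra. The size rests on assumed food-effect heterogeneity, the CV definition, the choice of test and 14 completers.

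A reader might infer that correcting the covariance makes the microbiome P values trustworthy, or that the trial's main conclusions are at risk. Neither follows. Same-data screening remains a separate and possibly larger source of false positives. The analysis is labelled exploratory, and no PBGP or iAUC estimate, individual WGRS or population-level result depends on it.

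**What to change.** Under Exploratory analysis, replace the random intercept by a compound-symmetric (or unstructured) residual covariance within participant that is allowed to be negative. This keeps the species and covariate main effects.

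Two alternatives leave the main-effect model in place and test the interaction separately:
- a second model with participant as a fixed effect; or
- permutation of whole microbiome profiles between participants, with the Spearman and LASSO screen repeated in every permutation. This option also addresses the screening.

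Participant fixed effects should not simply be put into the single planned model. Baseline microbiota and all the listed covariates are constant within a participant, so their main effects could no longer be estimated, and the protocol wants those too.

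The cost is a short change to plan and code, slightly larger interaction P values, and a second model if participant fixed effects are used. No new data are needed. If only the covariance is changed, the report should say that the P values are still not adjusted for the screening.

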### Patient and public involvement statement

In this study, patients and/or the public were not involved in the design, recruitment, or implementation of the experiment.

### Ethics approval and dissemination

The study protocol was approved by the Ethics Committee of the Inner Mongolia Nutrition Society. Our findings will be published in peer-reviewed journals or presented at international conferences. The full study protocol, anonymized participant-level data sets, and statistical code used to generate the results will be made available upon request from the corresponding author after the completion of the trial.

## Discussion

This study is designed to investigate the differences in PPGR among patients with diabetes consuming various staple foods using a series of *N*-of-1 trials. Real-time glucose fluctuations will be monitored via CGM as participants consume different staple foods. Bayesian multiple comparisons, in conjunction with a weighted averaging method, will be used to provide personalized dietary recommendations for each patient with diabetes, based on their WGRS on each staple food. Additionally, the study will explore the role of the gut microbiome in mediating glucose response variability. The results are expected to offer novel insights into personalized nutritional interventions for the management of diabetes.

There are significant differences in PPGR to different staple foods, primarily due to variations in their GI, which in turn affect individual PPGR. According to the 2021 International Glycemic Index and Glycemic Load Tables, there is substantial variation in the GI values among different staple foods [31]. In this study, 5 staple foods have been selected to represent either varying degrees of process on the same grain (refined rice, germ rice, and brown rice) or the different grains prepared using similar methods (rice noodles and pasta). The differing degrees of rice processing are known to influence the glycemic response by assessing GI. Refined rice, due to its rapid digestion and absorption, is a high GI food, resulting in a rapid rise in blood glucose concentrations postconsumption [32]. In contrast, brown rice, which retains more fiber, vitamins, and minerals, is digested more slowly, leading to less pronounced postprandial glucose fluctuations. Epidemiologic evidence has suggested that a high intake of refined rice was significantly linked to an increased incidence and mortality from T2DM, whereas intake of unrefined grains like brown rice was associated with reduced risk of T2DM [33,34]. A study using CGM to measure the 24-h glucose response to a high-fiber white rice diet among Asian Indian participants found that the average 24-h glucose response to high-fiber white rice was significantly lower than that to regular white rice [35]. A meta-analysis of randomized controlled trials indicated that pregerminated brown rice, in comparison with brown rice, had superior effects on lipid profiles and fasting blood glucose concentration [36]. Another meta-analysis reported that brown rice significantly influenced weight management in individuals with prediabetes and T2DM [37]. These findings highlight the importance of brown rice in controlling weight, reducing risk of diabetes, and improving overall metabolic health.

However, GI values of staple foods exhibit considerable variability among individuals, which poses a challenge to the universality of a standardized GI reference. Studies have shown that the SD of GI values within individuals and between individuals can reach 20%–25%, indicating that the same food can elicit significantly different blood glucose responses across different individuals. This suggests that the same food can elicit substantial differences in blood glucose responses across individuals. Therefore, this study aimed to address the variability in PPGR through an *N*-of-1 trial, exploring the specific impact of various staple foods on postprandial glucose load in patients with diabetes and identifying key factors that regulate these individual differences through gut microbiota analysis.

GI calculation typically relies on a relatively fixed blood glucose response curve, assuming data follows a normal distribution. However, this assumption is often not valid in practice. At the population level, GI involves ratios, which are often skewed or multimodal, rather than normally distributed, potentially affecting its reliability and validity. Unlike population-average GI, WGRS uses a Bayesian model to analyze the posterior probability of glucose fluctuations for each staple food, incorporating the CV of these differences as weights for a weighted average of the posterior probabilities. This approach integrates both the magnitude and stability of glucose fluctuations, offering a more accurate reflection of an individual’s blood glucose response to different staple foods in real-world settings.

Although CGM provides critical insights into dynamic glycemic responses, several technical considerations merit attention. First, the inherent physiological delay (5–15 min) between interstitial fluid glucose measurements and blood glucose measurements may cause a lag in detecting PBGP but does not systematically affect the relative differences in glycemic responses across interventions. Although the CGM devices used in this study showed slightly reduced accuracy in the hypoglycemic range, their reliability in the hyperglycemic range remained robust, ensuring dependable detection of primary end points in patients with T2DM [38]. Furthermore, as CGM accuracy declines over time, the replacement of sensors every 12 days in this study, coupled with a replicated crossover *N*-of-1 design, ensured a balanced distribution of residual drift across interventions. To account for potential individual-level random errors introduced by CGM, the Bayesian model incorporated individual-level variability through random effects, integrating uncertainty into posterior estimates. Although this protocol incorporates multiple rigorous measures to control potential confounding factors such as physical activity, dietary variations, and medication adherence, it is important to acknowledge that unquantified physical activity, chronic stress, or dietary changes on nontest days may introduce residual confounding effects, potentially influencing the interpretation of individual glucose responses. Future studies will leverage wearable devices for activity tracking, meal photography records and standardized dietary logs to further enhance precision.

This study uses an *N*-of-1 trial design to address the high individual heterogeneity in glycemic responses in diabetes management. Traditional research designs, based on population-average effects, often provide 1-size-fits-all dietary recommendations, overlooking the significant impact of biological differences, behavioral and lifestyle factors, and environmental influences on individual glycemic responses [39,40]. The *N*-of-1 design, through repeated and randomized within-individual crossover interventions, quantifies personalized responses of the same patient to different staple foods, enabling the formulation of dietary strategies based on the patient’s multidimensional characteristics. However, the broader application of the *N*-of-1 design requires balancing individualization with generalizability. Although this study aggregates individual data using Bayesian models to explore population trends, the generalizability of the conclusions remains limited by sample characteristics (e.g., sample specificity, staple food types, and processing methods) and external variables not fully controlled (e.g., physical activity, environmental stress). Future research could first use *N*-of-1 trials to identify response prototypes (e.g., microbiome-driven, insulin-sensitive, and lifestyle-dependent) and then validate subgroup-specific interventions through targeted randomized controlled trials, thereby balancing precision and scalability, and offering new insights for individualized interventions in diabetes management.

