### Study procedures

The study scheme is outlined in Figure 1. The study consists of 3 periods, each of which comprised 5 test days. On each test day, a different test diet will be consumed for breakfast. Within each period, the 5 test diets will be administered in a randomized sequence. By referring to the washout period duration (48 h) in previous studies by Zavitsanou et al. [21] and considering that key indicators such as postprandial blood glucose-related parameters can return to baseline concentrations within 2–3 d (thus effectively eliminating the residual effects of the dietary used in the previous test), a 3-d washout period was set between each test in this study. During the washout period, subjects were instructed to maintain their regular dietary habits [21,22]. To ensure consistency across test diets and to minimize the impact of prior dietary intake, participants will be advised to restrict their consumption of high-protein, high-fat, and high-fiber foods on the day preceding the test day. Additionally, they will be provided with a balanced dinner on the evening before the test day and will be required to fast for 12 h prior to the test diet. They will also be instructed to avoid strenuous physical activity and alcohol consumption on the day before the test day, with this requirement reinforced through both in-person and WeChat-based instructions. Except for the differences in the random allocation sequence of the 5 test diets, the other study procedures across the 3 periods are identical, such as blood glucose monitoring, safety evaluation, duration of the washout period, and provision of balanced dinners.

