### Randomization

The randomization process for the trial will be conducted by a statistician who is not involved in the data analysis to ensure impartiality. Allocation concealment will be achieved using sequentially numbered, opaque, sealed envelopes. The test diets will be designed in alphabetical letters. A random sequence will be generated using R software (R Foundation), with each participant’s order being independently randomized for each period. The order will be provided directly to the food preparation staff, who have no involvement in data collection and analysis. This study strictly implemented analyst blinding. Specifically, the statisticians responsible for data analysis remained completely unaware of which specific staple foods the letter codes represented until the final analysis was completed, and the results were locked.

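### The design balances sensor drift across foods only in expectation, not within a participant as the Discussion claims, and Equation 1 omits the period in which foods are randomised; the cost is precision, not bias

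*Protocol article*

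**What the plan says.** The Discussion concedes a time trend in the monitor ("as CGM accuracy declines over time"). It then states that "the replacement of sensors every 12 days in this study", combined with the replicated crossover, "ensured a balanced distribution of residual drift across interventions". It adds that random effects at the level of the individual take up the remaining monitor error.

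The schedule is under Study procedures: "The study consists of 3 periods, each of which comprised 5 test days", and "a 3-d washout period was set between each test in this study". Randomization has each participant's "order being independently randomized for each period", and states no restriction tied to the sensor or its age.

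Equation 1, under Individual-level N-of-1 trial analysis, is written out in full. It contains an intercept, one effect per food and a normal error. The population model is given in words only: "Individual regression models will be linked using a random-effects model". No period, sensor or time term is named there.

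**The concern.** A claim of realised balance needs the schedule to deliver it. If a sensor lasts for fewer tests than there are foods, and sensors change inside periods, some foods will by chance be tested more often on fresh sensors and others on old ones, or on different sensors altogether. The safeguard that the Discussion cites works at the wrong level: a participant effect is constant within a person, whereas the sensors differ within a person.

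This matters most for the individual contrasts and the weighted glycemic response score, where each food has only 3 observations and there is no averaging over participants. Separately, foods are randomised within period, so period is the block, and Equation 1 does not analyse by it. Any variation between periods then goes into the residual.

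**Working it through.** The claim about drift is qualitative, so there is no stated figure to reproduce.

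**Inputs from the protocol.** 3 periods × 5 test days = 15 tests; 3-day washout; 12-day sensors; within-individual SD 1.2 mmol/L; minimum clinically important difference (MCID) for peak glucose 0.78 mmol/L; n = 14 (Sample size estimation). **Assumptions, because the document gives no figures:** between-sensor SD, drift per day and between-period SD, each shown as a range.

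**1. Tests per sensor.** Reading the washout as 3 clear days gives one test every 4 days, so 12/4 = 3 tests per sensor and 5 sensors for 15 tests. Reading it as one test every 3 days gives 12/3 = 4 tests per sensor. Both are below 5.

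**2. Sensor age within a participant.** With 4-day spacing, the first sensor fitted at test 1 and no gap between periods, sensor age in days at the 15 tests is 0, 4, 8, 0, 4 | 8, 0, 4, 8, 0 | 4, 8, 0, 4, 8. The sample variances of age within the three periods are 11.2, 16 and 11.2. The difference in mean sensor age between two foods has expectation 0 and variance 2 × (11.2 + 16 + 11.2)/9 = 8.53, so its SD is 2.9 days. In 200,000 simulated participants, a given pair differed by 4 days or more in 26%, and all five foods had equal mean sensor age in about 0.6%.

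**3. Sensor offset in an individual contrast.** The chance that two foods share a sensor within a period is 0.4, 0.3 and 0.4 for the three periods. With sensor SD s, the added variance is s² × 2 × (0.6 + 0.7 + 0.6)/9 = 0.422 s², so the added SD is 0.65 s. The sampling SE is 1.2 × √(2/3) = 0.98.

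| Assumed sensor SD (mmol/L) | Added SD | Total SD = √(0.98² + added²) | Group level, added/√14 |
|---|---|---|---|
| 0.3 | 0.19 | 1.00 | 0.05 |
| 0.5 | 0.32 | 1.03 | 0.09 |
| 1.0 | 0.65 | 1.18 | 0.17 |

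**4. Drift.** Assumed linear drift of 0.05, 0.10 or 0.20 mmol/L per day, times 2.92 days, adds an SD of 0.15, 0.29 or 0.58 to an individual contrast. Divided by √14, this is 0.04 to 0.16 at group level.

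**5. Validity of the food-only interval.** With 15 tests per person, SD 1.2, drift 0.1 per day and sensor SD from 0.3 to 1.0, a 95% t interval from the food-only model (standing in for noninformative priors) covered the true contrast in 95% to 96% of simulated participants.

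**6. Omitted period.** The food-only residual has 15 − 5 = 10 df: 8 with mean square 1.44 and 2 for period with expected mean square 1.44 + 5σ², where σ is the between-period SD. The average is 1.44 + σ². Adding period leaves 8 df and raises the t multiplier from 2.228 to 2.306, a factor of 1.035.

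| Assumed σ (mmol/L) | √(1.44 + σ²)/1.2 | Divided by 1.035 | Net excess width |
|---|---|---|---|
| 0.3 | 1.031 | 0.996 | about 0% |
| 0.5 | 1.083 | 1.047 | about 5% |
| 0.8 | 1.202 | 1.161 | about 16% |

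**The case against.** Three stronger readings are tempting, and the documents support none of them.

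- *Food is confounded with sensor, so the food contrasts are biased.* Order is randomised independently in each period, so the expected difference in sensor age or offset between foods is zero. The 0.6% figure shows how rarely exact balance occurs; it does not measure harm.
- *The individual intervals are invalid.* Omitted sensor variation enters the residual and widens the interval. Coverage stays at 95% to 96% (step 5).
- *Leaving out period distorts the estimates.* Each food occurs once per period, so the food point estimates are the same with or without the term. Nor is there a flat 20% penalty on width: 1.202 is the gross ratio at σ = 0.8 only, and at σ = 0.3 nothing is gained.

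Other limits also stand. A constant additive offset cancels in the incremental AUC, which is measured from the pre-meal value, so the offset argument concerns peak glucose only. Part of the sensor noise may already be inside the 1.2 mmol/L. The exact map of tests to sensors is inferred, because insertion timing and any gap between periods are not stated; that a sensor covers fewer than 5 tests holds on both readings of the washout. The population model is described in words only, so no more can be said than that no such term is named, and sensor covariates are a detail that an analysis plan could supply.

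What the objection does not reach is that the Discussion asserts a balance the schedule does not deliver, names a safeguard that cannot work between a person's own sensors, and sits beside a written-out Equation 1 that omits the randomisation block.

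**Conclusion.** The point holds as one of precision and accurate description. Drift and sensor offset are balanced across foods in expectation, not within a participant, and participant-level effects cannot remove differences between that participant's sensors.

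The individual peak-glucose contrasts carry the cost. Relative to the 0.98 sampling SE, total SD rises by about 2%, 5% or 20% at assumed sensor SDs of 0.3, 0.5 or 1.0 mmol/L. Group-level error, at most 0.17 mmol/L over the ranges shown, is small beside the MCID of 0.78. Omitting period costs about 0% to 16% in individual interval width over assumed between-period SDs of 0.3 to 0.8.

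All of these sizes rest on assumed sensor, drift and period variation, and the sensor figures also rest on a regular 4-day cycle. With 3-day spacing they are nearly the same.

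**What to change.** - Add period, as the randomisation block, to Equation 1 and to the population model.
- In the population model only, add a sensor-within-participant random intercept and one wear-day slope common to all participants. Do not add these as fixed terms to Equation 1: with period, sensor and wear-day in it, 15 − 12 = 3 residual df remain, and the 95% interval for a contrast roughly doubles in width (about 4.7 to 9.3 mmol/L at sensor SD 0.5).
- Keep the separate individual analysis as planned, and report individual contrasts from the extended population model as a sensitivity analysis. Those estimates are shrunken, so replacing the individual analysis with them would change the weighted glycemic response score.
- Reword the Discussion to say that drift is balanced across foods in expectation, and drop the suggestion that individual-level random effects deal with differences between sensors.

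**Cost.** Two residual df per participant for period; at a between-period SD near 0.3 this buys nothing. Sensor replacement dates must be available for each participant, and the document does not say where they are recorded. No new measurements are needed.
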